## Abstract

**Background:**

In blended therapy, face-to-face psychotherapy and Internet-based interventions are combined. Blended therapy may be advantageous for patients and psychotherapists. However, most blended interventions focus on cognitive behavioral therapy or single disorders, making them less suitable for routine care settings.

**Methods:**

In a randomized controlled trial, we will compare blended therapy and face-to-face therapy in routine care. We intend to randomize 1152 patients nested in 231 psychotherapists in a 1:1 ratio. Patients in the blended therapy group will receive access to a **t**herapeutic **on**line **i**ntervention (TONI). TONI contains 12 transdiagnostic online modules suited for psychodynamic, cognitive behavioral, and systemic therapy. Psychotherapists decide which modules to assign and how to integrate TONI components into the psychotherapeutic process to tailor treatment to their patients’ specific needs. We will assess patients at baseline, 6 weeks, 12 weeks, and 6 months. Patients enrolled early in the trial will also complete assessments at 12 months. The primary outcomes are depression and anxiety at 6-month post-randomization, as measured by PHQ-8 and GAD-7. The secondary outcomes include satisfaction with life, level of functioning, personality traits and functioning, eating pathology, sexual problems, alcohol/drug use, satisfaction with treatment, negative effects, and mental health care utilization. In addition, we will collect several potential moderators and mediators, including therapeutic alliance, agency, and self-efficacy. Psychotherapists will also report on changes in symptom severity and therapeutic alliance. Qualitative interviews with psychotherapists and patients will shed light on the barriers and benefits of the blended intervention. Furthermore, we will assess significant others of enrolled patients in a sub-study.

**Discussion:**

The integration of online modules which use a common therapeutic language and address therapeutic principles shared across therapeutic approaches into regular psychotherapy has the potential to improve the effectiveness of psychotherapy and transfer it into everyday life as well help save therapists’ resources and close treatment gaps. A modular and transdiagnostic setup of the blended intervention also enables psychotherapists to tailor their treatment optimally to the needs of their patients.

**Trial registration:**

German Clinical Trials Register (DRKS) DRKS00028536. Registered on 07.06.2022.

## Administrative information

Note: The numbers in curly brackets in this protocol refer to the SPIRIT checklist item numbers. The order of the items has been modified to group similar items (see http://www.equator-network.org/reporting-guidelines/spirit-2013-statement-defining-standard-protocol-items-for-clinical-trials/).

## Introduction

### Background and rationale {6a}

Over the course of 12 months, about one-third of Germans meet the criteria for at least one mental disorder—of which nearly 50% have more than one mental disorder [1]. High prevalence and comorbidity rates offset significant treatment gaps and waiting times to access psychotherapy [2, 3]: Less than 25% of patients seek treatment, and if they do, they are faced with waiting times of about 5 months before starting psychotherapy in German outpatient routine care.

Blended therapy may constitute a promising way to close treatment gaps. In blended therapy, Internet-based interventions and face-to-face psychotherapy are combined in different ways [4, 5]. Internet-based interventions can serve as an add-on to psychotherapy without being integrated into face-to-face therapy [5]. Internet-based interventions can also be an integral part of face-to-face therapy. For example, topics and exercises are discussed in in-person sessions, and patients then continue to work on these topics online. The results from a systematic review suggest that blended therapy may save clinician time, lower dropout rates, and maintain changes achieved during psychotherapy [5]. However, while the effects of blended treatments are promising, the overarching potential of blended therapy is difficult to determine since blended treatments encompass such a wide array of different setups [5]. In addition, direct comparisons between face-to-face and blended therapy in routine care are still sparse. Those studies that compared both treatment formats directly yielded small to medium between-group effects in favor of blended therapy [6]. Blended treatments combine the benefits of Internet-based and in-person treatments: On the one hand, they provide the flexibility and potential to integrate psychotherapy into the everyday lives of patients inherent to stand-alone Internet-based interventions. Additionally, as part of the treatment process may be conducted via online self-help materials, blended interventions have the potential to save clinician time. On the other hand, they offer the personal contact of in-person psychotherapy that may capitalize on in-session processes and respond to crises more adequately [7, 8].

So far, blended therapy is not implemented in outpatient routine care in Germany. Several factors constitute barriers to the implementation of blended therapy. First and foremost, the needs of practicing psychotherapists and their patients and existing blended interventions are not aligned: The majority of Internet-based interventions focus on cognitive behavioral therapy (CBT) [9, 10], target anxiety and depression [11], and allow for little flexibility and tailoring.

The strong CBT focus does not reflect the therapeutic orientation of psychotherapists practicing in routine care in Germany: More than 40% of psychotherapists have a different therapeutic orientation than CBT. The emergence of psychodynamic Internet-based interventions also underlines that other therapeutic principles besides CBT can successfully be delivered over the Internet [12]. However, instead of developing interventions specific to one therapeutic approach, it may be plausible to develop and deliver Internet-based interventions in an integrative manner that uses a common therapeutic language. This would ensure the uptake of Internet-based intervention by a wider range of psychotherapists in routine care. Besides, many psychotherapists integrate elements across different approaches of therapy, the psychotherapeutic practice of different approaches is not as distinguishable as one might expect [13–15], and different approaches share the same mechanisms of change [16, 17].

The focus on anxiety and depression neglects other prevalent mental disorders, such as the remainder of the internalizing (e.g., eating disorders and sexual dysfunctions), the whole externalizing spectrum (e.g., substance-related disorders), and thought disorders [18]. In addition, Internet-based interventions integrated into outpatient routine care need to target comorbidity appropriately, as those patients who use mental health services are typically those with more than one diagnosis [3]. For psychotherapists to embrace and integrate Internet-based interventions into their clinical practice, interventions need to be customizable and flexible. Psychotherapists emphasize that they need to be able to select and individualize treatment elements and choose how to integrate Internet-based interventions into their practice [19].

A transdiagnostic and modular blended intervention that uses a common therapeutic language has the potential to overcome these barriers. Through means of a formative research process with psychotherapists and patients, we developed existing transdiagnostic online modules into such a blended intervention using a common therapeutic language. Therapeutic online intervention (TONI) provides psychotherapists with online modules that they can integrate into their treatment to flexibly blend online components and face-to-face sessions. The aim of the current study is to investigate the effectiveness of blending TONI and face-to-face psychotherapy in routine care in Germany. For this purpose, blended psychotherapy is compared to regular face-to-face psychotherapy in routine care.

### Objectives {7}

This randomized controlled trial (RCT) evaluates whether providing psychotherapists access to online modules that they can integrate into psychotherapy benefits patients and psychotherapists. We hypothesize that patients in the blended therapy condition show larger reductions in symptoms over time than participants that solely receive face-to-face therapy. We hypothesize this effect to be small. We will investigate the treatments’ effects on the level of functioning, satisfaction with life, transdiagnostic symptoms, and personality. In addition, length of treatment, satisfaction with treatment, and negative effects are considered. We will investigate which moderators and mediators are relevant for treatment effects. We will also explore how psychotherapists and patients engage with the intervention and whether the extent of usage of the intervention moderates effects. In addition, qualitative interviews with psychotherapists and patients will shed light on the barriers and facilitators of the intervention. Furthermore, we will assess significant others of enrolled patients in a sub-study.

### Trial design {8}

A parallel-group, two-arm randomized controlled superiority trial compares the effectiveness of blended therapy to face-to-face therapy in Germany with a 1:1 allocation ratio. Quantitative and qualitative data will determine the effect of enabling psychotherapists to add online elements to their face-to-face therapy in routine outpatient care. This trial protocol is reported following the SPIRIT guidelines. The study has been registered in the German clinical trial register under DRKS00028536. The ethics committee of Psychologische Hochschule Berlin (EK202121) approved the trial.

## Methods: participants, interventions, and outcomes

### Study setting {9}

The study is jointly run by Freie Universität Berlin and Psychologische Hochschule Berlin. We will recruit psychotherapists in German routine care to participate in the study. They in turn will recruit their patients at the beginning of psychotherapy. Psychotherapists as well as patients and their significant others will complete the assessments on the TONI platform. In addition, we will conduct telephone interviews with a selection of psychotherapists and patients.

### Eligibility criteria {10}

All psychotherapists, irrespective of psychotherapeutic approach, are eligible for inclusion if they (a) take part in contractual routine psychotherapy in Germany and (b) have Internet access in their practice. Their patients who (a) are over 18 years old, (b) have access to the Internet, (c) have sufficient German language skills, and (d) can read and write are eligible for inclusion. Psychotherapists use these inclusion criteria to decide whom to invite to participate in the study. In addition, psychotherapists and patients have to verify during the registration process that these inclusion criteria apply to them. Since this is a naturalistic trial in routine care, there are no exclusion criteria regarding diagnoses or symptom severity.

### Who will take informed consent? {26a}

Psychotherapists, patients, and significant others of patients will give written informed consent online.

### Additional consent provisions for collection and use of participant data and biological specimens {26b}

Participants who take part in the interviews will consent to their participation via e-mail. No biological specimens will be collected.

### Interventions

#### Explanation for the choice of comparators {6b}

Blended therapy — the integration of Internet-based interventions in face-to-face therapy — is a promising treatment option regarding clinical effectiveness and utility. Moreover, the implementation may also help to close treatment gaps in routine care, e.g., by intensifying treatment effects. For this purpose, blended therapy is compared to regular face-to-face psychotherapy — the current gold standard of mental health care. The main hypothesis is that blended therapy will demonstrate superiority to face-to-face psychotherapy in reducing symptom distress in patients in routine care.

### Intervention description {11a}

TONI is a digital toolbox comprising modules and self-tracking tools that can be used to blend Internet-based components and face-to-face psychotherapy. TONI consists of 12 transdiagnostic modules (see Table 1 for a description of the intervention components). Every module consists of two to seven chapters. Psychotherapists can individualize modules by selecting chapters and choosing which TONI components to integrate when into their treatment. Patients can also request access to modules. In addition to the modules, TONI includes several tracker tools that allow patients to track their distress, mood, activity, sleep, craving, or individual problems which they can share with their therapist. Patients can also use a diary and have access to an “emergency kit” with emergency contacts and skills to apply during a crisis. Optionally, psychotherapists can choose to communicate with their patients via the platform.

**Table 1 Tab1:** Intervention components

Module	Description of major concepts and components
Development	In chapter 1, patients learn about the biopsychosocial etiological model of distress and reflect on factors that may influence and maintain their symptoms. In chapter 2, patients reflect on their own biographical history and identify possible commonalities between fluctuations in their mental health. In chapter 3, patients develop a genogram of their family history and relations to identify intergenerational patterns that may influence them in their present.
Values and goals	In chapter 1, patients reflect on their motivation for change and identify barriers to change they have encountered in the past. Chapter 2 helps patients to identify their personal values that guide them through life. In chapter 3, patients reflect on the goals they want to work towards in therapy.
Mindfulness	In chapter 1, patients are introduced to the concept and components of mindfulness. Chapter 2 offers a selection of different internal and external mindfulness-based exercises.
Getting active	In chapter 1, patients learn about the relationship between activity and mood. In chapter 2, they reflect on which activities give them fulfillment and enjoyment. In chapter 3, they work towards implementing more activities in their everyday life.
Thoughts	In chapter 1, patients learn about the relationship between thoughts and emotions. In chapter 2, they identify how their life story shaped their thoughts. They identify and challenge their beliefs. In chapter 3, patients practice mentalization and take different perspectives.
Understanding feelings	In chapter 1, patients learn about feelings and reflect on their stance towards emotions. Chapter 2 focuses on the messages behind feelings. In chapter 3, patients reflect on how their life story shapes their emotional experience.
Dealing with feelings	In chapter 1, patients learn how to tolerate emotions. In chapter 2, patients learn more about avoidance/defense mechanisms and experiment with trying out new reactions.
Self-worth and strengths	Chapter 1 introduces the concept of self-worth, and patients reflect on the standards they set for themselves. Chapter 2 focuses on how patients can treat themselves with more kindness and self-compassion. Chapter 3 focuses on establishing which strengths and resources patients have and how they can utilize them more.
Communication	Chapter 1 introduces patients to the different meanings that messages can convey. In chapter 2, patients identify their communication patterns and reflect on their relationships with others. In chapter 3, patients learn how to communicate their needs and wishes in a nonviolent way.
Body and well-being	This module contains different chapters that are relevant for healthy living: a chapter on the relationship between body and mind, eating and body image, sleep, movement, pain and bodily complaints, sexuality, and stress. All of them include psychoeducation on the topic and exercises to try out new ways of dealing with these topics.
Addictive substances and behaviors	In chapter 1, patients are introduced to the core concepts of substance- and non-substance-related use and reflect on whether they have any wishes for change in these areas. Chapter 2 encourages patients to reflect on the pros and cons of engaging in their substance use/ addictive behavior. Chapter 3 focuses on craving and how to deal with craving. Chapter 4 focuses on relapse prevention and how to deal with relapses.
Collaboration	This module is targeted at a patient’s significant other. Chapter 1 focuses on how the significant other deals with his or her own mental well-being. In chapter 2, significant others are introduced to some of the basics of therapy and emotional well-being. Chapter 3 offers exercises that patients and their significant other can work on together, e.g., acknowledging aspects they appreciate about each other or reflecting which difficulties they have mastered in the past together.

We developed TONI by means of a formative research process including psychotherapists from all recognized therapeutic approaches in Germany (psychodynamic, cognitive-behavioral, and systemic) and patients with lived experience.

### Criteria for discontinuing or modifying allocated interventions {11b}

TONI automatically logs adherence and engagement with the online modules. We will report adherence and usage metrics. Therapists decide to what extent online modules are assigned and integrated based on the course of therapy. Therapists have access to certain usage metrics which allows them to monitor their patients’ platform usage (e.g., last login more than 4 weeks ago, % of modules completed) and address potential issues in in-person sessions or via the integrated messenger. In addition, therapists can monitor symptom progression and session ratings and adjust the intervention if necessary. Patients will be invited to assessments even if they drop out of therapy or discontinue working on modules.

### Strategies to improve adherence to interventions {11c}

Psychotherapists are informed about ways to integrate TONI into therapy and sessions in video tutorials at the beginning of the trial and in a study manual that they receive via mail. To ensure that psychotherapists invite patients to participate in the study and use TONI, they will receive a monetary compensation for the tutorials, which is paid out after including three patients, and for the usage of TONI for every patient in the blended care group. The platform automatically logs engagement with TONI. This includes numbers and duration of logins, modules/chapters assigned and completed, and messages exchanged. Patients receive e-mail notifications if a new module or assessment is available to them. Both patients and therapists also have a newsfeed on their dashboard notifying and reminding them about tasks or events.

### Relevant concomitant care permitted or prohibited during the trial {11d}

n/a: There are no prohibited additional interventions specified as this is a trial conducted in routine care. We will assess medication use and mental health care utilization to determine additional mental health care utilization.

### Provisions for post-trial care {30}

n/a: There is no ancillary post-trial care or compensation. Patients are enrolled in routine psychotherapy during the study duration.

### Outcomes {12}

Patient outcome measures consist of self-reported questionnaires, which are assessed at baseline (*t*_0_), after 6 weeks (*t*_1_), after 12 weeks (*t*_2_), and after 6 months (*t*_3_). Patients who are enrolled early and are able to complete a 12-month assessment within the duration of the project will also complete a 12-month follow-up assessment (*t*_4_). Patients who receive blended therapy will also complete an assessment for every in-person session. Psychotherapists will provide sociodemographic data regarding their own person at baseline and then rate their patients and therapeutic alliance throughout treatment in both groups. All questionnaires will be presented via the platform that also hosts the intervention. See Table 2 and the “Data collection and management” section for details of measurements at all time points.

**Table 2 Tab2:** Schedule of enrollment, interventions, and assessments

**Assessment/activity**		**Enrollment**	**Allocation**	**Post-allocation**				
		***-t***_**1**_	**0**	***t***_**1**_	***t***_**2**_	***t***_**3**_	***t***_**4**_	**Others**
**Enrollment**	**Eligibility screen**	X						
	**Informed consent**	X						
	**Allocation**		X					
**Interventions**	***Treatment as usual***							
	***Blended therapy***							
***Assessment of therapists***	Sociodemographic data	X						
	BFI-10	X						
	CGI-S	X		X	X	X	X	
	CGI-C			X	X	X	X	
	WAI			X	X	X		
	Description of patient problems	X						
	Expectation of outcome and dropout	X						
	Perceived similarity	X		X				
	NEQ					X		
	SUS					X		
	Usage time					X		
***Assessment of patients***	Sociodemographic data	X						
	ACE	X						
	Perceived similarity	X		X				
	Expectation of outcome and dropout	X						
	PHQ-ADS (PHQ-8 and GAD-7)	X		X	X	X	X	
	SWLS	X		X	X	X	X	
	AQoL-8D	X		X	X	X	X	
	EDE-Q8	X				X	X	
	DUDIT-C	X				X	X	
	AUDIT-C	X				X	X	
	MGH	X				X	X	
	PID5BF +	X				X	X	
	OPD-SFK	X				X	X	
	FIMPsy	X				X	X	
	NEQ					X		
	CSQ-8					X		
	Change rating					X	X	
	SUS					X		
	ASKU	x		X	X	X	X	
	MHSES	x		X	X	X	X	
	Empowerment					X		
	TAI			X	X	X		
	WAI-SR			X	X	X		
	CPPS			X	X			
	MULTI			X	X			
	SRS/ORS (only BC)							Weekly
***Assessments of significant others***	Sociodemographic data	X						
	Expectation of outcome and dropout of patient	X						
	PHQ-ADS (GAD-7 and PHQ-8)	x				x		
	Rating of distress of patient (GAD-7 and PHQ-8)	x				x		
	IEQ	x				x		
	Therapy-associated changes					x		
	NEQ					x		

#### Participant timeline {13}

Figure 1 depicts a CONSORT flow diagram. We will direct psychotherapists interested in participating to a study website that provides further information on the trial. Therapists willing to participate can sign up for participation and give electronic written informed consent. Once registered, therapists recruit participants within their pool of patients who are looking to start therapy. If patients are interested, they can sign up on the platform via a personalized link or code that they receive from their psychotherapist. Once patients have entered the platform, they will give electronic written informed consent, complete questionnaires, and are randomized to one of two groups: blended therapy (face-to-face therapy plus TONI) or face-to-face therapy.

**Fig. 1 Fig1:**
[figure not shown]
CONSORT flow diagram

#### Sample size {14}

The sample size calculation is based on a clinically relevant additive effect with an effect size of *d* = 0.2 in favor of blended therapy [20, 21]. To detect this effect in a randomized controlled trial with a t-test (alpha error level = 5%, two-sided) for independent samples at 6 months post-randomization with a power of 80 percent requires 400 subjects per treatment group. Randomization occurs at the patient level, but patients are simultaneously nested in therapists. With an average of 25 new treatment cases per psychotherapist per year [22], we conservatively assume that an estimated minimum of 5 patients per psychotherapist agree to participate in the trial. To adequately address nesting, the therapist effect must be considered. Based on recent studies, we assume an intraclass correlation of 0.05 [23]. This results in a design effect of 1.2 [design effect = 1 + (*n*_*C*_ − 1) × ICC = 1 + (5 − 1) × 0.05 = 1.20]. Additionally, we estimate that 20% of patients will drop out of the study by the time of the post-treatment assessment [24]. Considering these factors results in a required sample of at least (400 × design effect × missing values = 400 × 1.2 × 1.2) 1152 patients (~ 231 psychotherapists).

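### The 20% dropout allowance is applied as ×1.2 rather than ÷0.8, so on the plan's own inputs the required total is 1200, not 1152; the cost is about one point of power

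*Protocol article*

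**What the plan says.** The whole derivation is printed in the protocol article under Sample size {14}. The test is a "t-test (alpha error level = 5%, two-sided) for independent samples at 6 months post-randomization", the effect is d = 0.2, and this "with a power of 80 percent requires 400 subjects per treatment group".

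Two inflations follow:

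- **Clustering.** The plan says "we conservatively assume that an estimated minimum of 5 patients per psychotherapist agree to participate in the trial". With an intraclass correlation of 0.05, the design effect is 1 + (5 − 1) × 0.05 = 1.20.
- **Dropout.** The plan says "we estimate that 20% of patients will drop out of the study by the time of the post-treatment assessment".

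The text continues "Considering these factors results in a required sample of at least" 1152 patients, or about 231 psychotherapists. The product shown is 400 × 1.2 × 1.2, in which the second 1.2 is the allowance for missing values. The Abstract (Methods) repeats the result as the enrolment target: "We intend to randomize 1152 patients nested in 231 psychotherapists in a 1:1 ratio".

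**The concern.** Dropout is given as a share of the patients who enter the trial, so 80% are expected to be retained. To end with a required number of analysed patients, that number has to be divided by 0.80, which is a factor of 1.25. The plan uses 1.20, so its total should fall short of its own target. The total is described as a minimum, it is the figure quoted in the Abstract, and the Discussion relies on it when it says that the trial can detect small differences. The derivation should therefore reproduce. At stake is whether 1152 delivers the stated 80% power and, if not, by how much it misses.

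**Working it through.** **Inputs**, all from Sample size {14}: two-sided alpha 0.05; power 0.80; d = 0.2; 400 per arm; 5 patients per psychotherapist; intraclass correlation 0.05; dropout 20%. Allocation is 1:1.

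**1. Base sample size.** For d = 0.2, two-sided 5% and 80% power, the exact t-test needs 393.4 per arm, so 394. The plan's 400 is this figure rounded up. Power at 400 per arm is 80.6% (exact t-test) or 80.7% (normal approximation).

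**2. Reproducing the plan's total.**
- Design effect: 1 + (5 − 1) × 0.05 = 1.20, so 400 × 1.20 = 480 analysed patients are needed per arm.
- Dropout as the plan applies it: 480 × 1.2 = 576 per arm.
- Total: 2 × 576 = 1152. Psychotherapists: 1152 / 5 = 230.4, so 231.

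The stated figures reproduce, but only with multiplication by (1 + 0.20).

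**3. Dropout covered by a factor of 1.2.** 1 − 1/1.2 = 16.7%.

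**4. What 1152 leaves after a 20% loss.**
- Analysed per arm: 576 × 0.8 = 460.8, against the 480 needed.
- Effective per arm at the plan's design effect: 460.8 / 1.2 = 384, against 400 (16 short, or 4%).
- Power at 384 per arm: 79.0% (exact t-test) or 79.1% (normal approximation).

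**5. Total with the dropout step done by division.**
- 2 × 400 × 1.2 / 0.8 = 1200 patients; 1200 / 5 = 240 psychotherapists.
- Difference from the plan: 48 patients and 9 psychotherapists.
- Starting from the unrounded minimum: 2 × 394 × 1.2 / 0.8 = 1182, still above 1152. Rounding up to 400 therefore does not absorb the slip.

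**6. Sensitivity to the cluster size.** If 20% of each psychotherapist's 5 patients are lost, about 5 × 0.8 = 4 are analysed.
- Design effect at 4: 1 + (4 − 1) × 0.05 = 1.15.
- Effective per arm: 460.8 / 1.15 = 400.7, with power 80.7% (exact t-test).
- Total needed: 2 × 400 × 1.15 / 0.8 = 1150, which 1152 meets.

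**The case against.** **Cluster size.** The strongest reply is step 6. The 5 patients per psychotherapist are those who agree to take part, so the cluster size is an enrolled one. Removing 20% of patients while keeping the design effect for 5 mixes two bases. Applied to the patients analysed, the plan's own formula brings 1152 back to target. This stands as arithmetic and shows that the number 1152 can be defended. It does not rescue the printed derivation, which fixes the design effect at 1.20 and never makes this argument.

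**Missing-data methods.** The section on missing data {20c} keeps all randomized patients by multiple imputation or full information maximum likelihood, with covariates. Patients who leave therapy are still invited to assessments ({11b}, {18b}). This may recover information, so 79% is a planning figure for an unadjusted t-test and not a forecast of the power of the primary analysis. The sample size calculation takes no credit for any of it, however.

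**Randomization within psychotherapists.** Implementation {16c} aims for each psychotherapist to treat patients in both groups, so a design effect above 1 is probably conservative and real power may be higher. That is a separate matter from the dropout step. How much higher depends on how far the treatment effect varies between psychotherapists, which the document does not give, so no figure is offered here.

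**Stronger readings.** A reader might infer that the trial is materially underpowered, or that neither 1152 nor 80% can be supported. The document does not bear this out: the miss is about one point on the plan's stated inputs, and none if the design effect is taken at the analysed cluster size. A reader might also count the printed product, which equals 576, as a second error. It is only notation: 400 is stated per group, and 2 × 576 is exactly 1152.

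**Conclusion.** The point holds as an arithmetic error with a minor effect. A 20% loss is assumed, but the factor used covers 16.7%. On the plan's inputs the minimum is 1200 rather than 1152, and 1152 gives about 79% power rather than 80%. This rests on four things: d = 0.2; an unadjusted t-test; 20% of randomized patients contributing no 6-month outcome; and the plan's design effect of 1.20 kept after dropout. If the last is relaxed to 1.15, the shortfall vanishes. A gap of one point is small beside the uncertainty in the effect size, the intraclass correlation and the dropout rate. The case for correcting it is that a headline figure described as a minimum does not follow from its own inputs.

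**What to change.** Keep enrolment at 1152. In Sample size {14}:

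- Write the dropout step as division by (1 − 0.20).
- Then do one of two things. Either restate the power of 1152 as about 79% at the stated design effect of 1.2, or say explicitly that the design effect is evaluated at about 4 analysed patients per psychotherapist (1.15), which gives about 401 effective patients per arm and about 80.7% power.
- As a clerical tidy-up, print the factor 2 for the two arms.

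The cost is one or two lines of text and, under the first option, one changed power figure. Recruitment, design and analysis are unaffected. The same wording should be carried into the results paper so that the multiplication is not repeated there.
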